**Research question 1: Evaluation of outpatient CBT-E as a standard treatment for AN**

Do adult AN patients provided with CBT-E treatment in a Norwegian outpatient setting show favorable pre-post changes, and are these sustained at 12 months after ending treatment? We expect changes to occur in the following areas: weight gain and eating-disorder pathology, depressive symptoms and depression, anxiety, general psychological impairment, and health-related quality of life.

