## Methods/Design

### Study design

The current project is an open, longitudinal treatment study undertaken in an ordinary clinical setting at a regional eating-disorder unit (Section for Eating Disorders, SED). All patients will receive a minimum of 40 sessions of outpatient CBT-E that cover the different treatment sessions described in the CBT-E manual for underweight patients [17], which is the standard treatment for AN at our unit. A control group without eating disorders will also be recruited.

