### Patient sample

All patients who agree to receive treatment for AN at the SED will be asked to participate in the study. Patients are referred to the clinic by general practitioners and secondary (specialist) health-care services. Written informed consent will be obtained after the patients have received written and oral descriptions about the study. During the past 2 years, 96 AN patients were offered treatment at the SED. We aim to include 100 patients in the current study. Analyses of statistical power showed that the proposed sample sizes in the different studies are sufficient.

The study will include patients aged >16 years who are suffering from AN, as diagnosed based on the DSM-5 (Diagnostic and Statistical Manual of Mental Disorders, Fifth Edition) [1] and confirmed with a clinical examination. Patients offered treatment at the SED have either at least one unsuccessful treatment attempt in a secondary health-care service unit or severe AN that is evaluated as not manageable in a secondary health-care service unit. Participation in the study will be offered to patients younger than 18 years if they do not fulfill the criteria for receiving FBT for AN [49]. Patients will be excluded from participation if it is deemed unsafe to manage them on an outpatient basis or have psychiatric comorbidity (as evaluated with MINI [50]) that precludes a focused eating-disorder treatment, such as psychosis or drug abuse. Patients who are not available to participate during the requested treatment period will also be excluded.

In line with clinical practice, patients will be withdrawn from outpatient treatment if they are unable to participate actively in the treatment program according to the judgement of the clinician, based on not attending sessions (more than three consecutive treatment sessions without giving notice) or not engaging in using the treatment tools (e.g. not self-monitoring).

Treatment at the SED is offered in a stepped care model, whereby patients participating fully in outpatient treatment but still not achieving the necessary changes will be offered a more-intensive treatment option (Intensive CBT-E) as inpatients or in day care. These patients will be included as a separate group in the analyses.

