	BAI	x			x	x	x	x
	RAND-36	x				x		x
	SCL-90-R	x				x		x
Treatment parameters	Measure of early adherence			x				
	WAI-S			x		x		
	Type of treatment (CBT-E or Intensive CBT-E)	x			x	x	x	x
	Active, finished, or dropped out	x			x	x	x	x
	Parallel psychological treatment (other diagnose)	x			x	x	x	x
Activity measures	Accelerometry	x				x		x
	Daily log of physical activity (over 7 days)	x				x		x
	EED	x				x		x
	CET	x				x		x
Stool sample in biobank	Bacteriological measures	x			x	x		x
	IBS self-report	x			x	x		x

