### Primary outcome measure

#### Eating Disorder Examination Questionnaire

The EDE-Q [55] is a 28-item self-report instrument designed to measure eating pathology. A recent review systematically studied the psychometric properties of the EDE-Q, and concluded that the instrument is reliable and valid for assessing eating-disorder symptoms [56]. The EDQ-E consists of four subscales: restraint, eating concern, shape concern and weight concern. The summation of the scores on all subscales produce a global EDE-Q score.

We will use a Norwegian translation that has Norwegian norms, good reliability, and expected correlations with BMI in a community sample [57, 58].

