## Discussion

Conducting studies in an ordinary health care setting poses both challenges and advantages. An advantage is the possibility to test how treatments evaluated in research clinics translate into an ordinary public hospital setting.

A challenge when implementing studies in an ordinary clinical setting is to secure the quality of the data collection and avoid missing data. The therapists have a busy schedule and assessments for the study need to be embedded into their daily routines and be experienced as meaningful for both therapists and patients. To secure this a detailed protocol for the data collection is written in co-operation with the therapists. Further, the therapists have been involved in designing the study through several meetings.

At 12-months follow-up the participants in the treatment study are compensated for their travel expenses for coming to the clinic to avoid this being a barrier for participating. The healthy weight controls likewise get their expenses covered as well as receiving a reward of 500 NOK (about 40 Euros).

Another aspect of implementing a treatment study into clinical practice is the question of patients receiving different treatments based on entering the study or not; and the need to follow national clinical guidelines for treatment. This makes a randomized controlled trial difficult to conduct in this setting. A waitlist condition also would prove ethically difficult because of the severity of the illness. Accordingly, in this study all patients receive the same treatment irrespective of study participation and there is no waiting-list or comparison group for the treatment condition. This constitutes a weakness when drawing conclusions based on treatment response.

To secure patient safety in cases of withdrawing from the study the routines are as follows: For patients deciding to leave the study, treatment continues. If the patient decides to end treatment pre-maturely they are referred back to their primary GP or to other relevant treatment. There is always an invitation to return to the eating disorder treatment at a later point of time if this is relevant and the patient wants to work in treatment again.

The longitudinal design of this study and the inclusion of a healthy control group are significant strengths that will contribute to a better understanding of AN pathophysiology, which could have implications for treatment efficacy.

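### Stepped-up patients form a separate analysis group defined by poor response; if the remaining outpatient group is taken to answer research question 1, its pre-post change is biased towards benefit

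*Protocol article*

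**What the plan says.** Research question 1 in the protocol article concerns outpatient treatment: "Do adult AN patients provided with CBT-E treatment in a Norwegian outpatient setting show favorable pre-post changes", and whether the changes last to 12 months after treatment. The primary outcome measure is the EDE-Q; BMI is secondary.

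Patient sample describes a stepped-care model in which "patients participating fully in outpatient treatment but still not achieving the necessary changes will be offered a more-intensive treatment option", namely Intensive CBT-E as inpatients or in day care. On the analysis it adds one sentence: "These patients will be included as a separate group in the analyses". Patients who do not engage fall under a different rule in the same section and are withdrawn from outpatient treatment.

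Three other places bear on this:

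- Study design says "All patients will receive a minimum of 40 sessions of outpatient CBT-E". The article does not say at what point in that course a transfer happens.
- Table 1 records "Type of treatment (CBT-E or Intensive CBT-E") at baseline and at each later main time point. BMI is also taken weekly, and the EDE-Q at baseline, 3 months, end of treatment and both follow-ups. Which end of treatment applies to a stepped-up patient is not stated.
- The Discussion confirms that "there is no waiting-list or comparison group for the treatment condition" and names this as a weakness.

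**The concern.** The separate group is not a baseline subgroup. A patient enters it by adhering to outpatient CBT-E and not improving enough. The patients left behind have therefore been selected, in part, on the outcome being measured. Their mean pre-post change estimates the change among those for whom outpatient treatment was judged sufficient or who left for other reasons. It does not estimate the change among patients who start outpatient CBT-E.

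In a randomised trial, a comparator arm handled the same way might share or expose such a selection. Here the pre-post change is all the evidence on effectiveness. The Discussion acknowledges the missing comparator but not this selection. At stake is what research question 1 can conclude about outpatient CBT-E as a standard treatment.

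**Working it through.** **The plan's own figure.** Power analyses gives d = 0.8, alpha 0.05, power 0.80 and correlation 0.50 between measurements, and reports 12 subjects for the effect of time. With correlation 0.50 the SD of the change equals the SD of the score, so dz = 0.8/√(2 × (1 − 0.5)) = 0.80. A one-sided paired t test then needs n = 12 (power 0.829). A repeated-measures F test with f = 0.4 and three time points also needs 12 (power 0.816). A two-sided paired t test needs 15. The 12 is thus reproduced by standard variants. It does not depend on how stepped-up patients are handled, but it supplies the 0.8 used below.

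**Inputs that the article does not give.** These are the share f who step up, and how far those patients change under outpatient treatment. Both are assumptions here.

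**Illustration A: 0.8 describes the patients who stay in the outpatient group.**

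Change in all starters = (1 − f) × 0.8 + f × d_s, where d_s is the outpatient change of stepped-up patients. The overstatement is f × (0.8 − d_s).

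- f = 0.10, d_s = 0.4: all starters 0.72 + 0.04 = 0.76; overstatement 0.04 SD.
- f = 0.20, d_s = 0.2: 0.64 + 0.04 = 0.68; overstatement 0.12 SD.
- f = 0.30, d_s = 0: 0.56 + 0 = 0.56; overstatement 0.24 SD.

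If step-up is decided mainly on weight, the EDE-Q change of stepped-up patients may lie closer to that of the rest. With f = 0.20 and d_s = 0.6, the overstatement is 0.20 × 0.2 = 0.04 SD.

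**Illustration B: 0.8 describes all starters.** This answers a different question and does not confirm A. Suppose the lowest fraction f step up on a score that correlates r with final outpatient change. The mean of those remaining rises by r × φ(z_f)/(1 − f) SD, which is 0.195r at f = 10%, 0.350r at 20% and 0.497r at 30%. Simulation agreed.

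- f = 10%, r = 0.3: +0.06, so 0.80 appears as 0.86.
- f = 20%, r = 0.5: +0.17, so 0.80 appears as 0.97.
- f = 30%, r = 0.8: +0.40, so 0.80 appears as 1.20.

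The shift is zero only if r = 0. A rule that selects on insufficient change makes that unlikely, at least for the outcome the clinicians look at. The model is rough: it takes the whole lower tail, whereas only fully participating patients step up.

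**Does significance turn on it?** Under Illustration A, no. At the lowest value, 0.56 × √100 = 5.6 standard errors with the planned 100 patients (taking the SD of change as 1). What is affected is the size of the effect.

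**The case against.** The strongest reply is that being included as a separate group is not the same as being removed. A reader might infer that research question 1 will be answered from the remaining outpatient patients only, so that the plan itself inflates the primary effect. The article does not say that. It sets out no analysis sets, its wording leaves room for an analysis of all starters, and an analysis plan that is not shown may contain one. This stands, and it is why the point is conditional.

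Two further inferences are also unsupported. One is that outpatient failure goes unrecorded. Treatment type is recorded at the main time points, BMI is taken weekly and there is a 3-month EDE-Q, so only a late EDE-Q before transfer may be missing. The other is that non-responders drop out of the predictor models; research questions 2 and 3 state no such restriction.

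Separation also has a sound purpose. Intensive CBT-E expects 1.0-1.5 kg gain per week over a standard 13 weeks, up to 13-19.5 kg if that rate lasted throughout (it applies only until normal weight is reached). Pooling values taken after such care would credit inpatient gains to outpatient treatment, which is also a bias towards benefit. This stands too, and the fix has to respect it.

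Finally, the magnitude is assumed. That is correct. What remains is that the only handling rule the article does state depends on the outcome, and that nothing in it says which population and which value answer research question 1.

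**Conclusion.** The point holds in conditional form. The separate group is formed after baseline by poor response, so an outpatient result without it is biased towards benefit, and no comparator would reveal this. The direction follows from the stated rule, provided that step-up is related to the outcome analysed.

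The size is not in the article. The 0.04-0.24 SD range rests on an assumed step-up share of 10-30%, an assumed outpatient change of 0-0.4 SD in those patients, and 0.8 SD in the rest. The EDE-Q effect would be at the low end or below if the decision rests mainly on weight. The documents do not support saying that the primary effect will be inflated, because they do not exclude an analysis of all starters.

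This should be fixed; confidence is moderate.

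**What to change.** 1. State that the primary population for research question 1 is all patients who start outpatient CBT-E, analysed together.
2. For the outpatient effect, use the last EDE-Q and BMI before transfer in stepped-up patients, so that inpatient gains are not credited to outpatient care. Weekly BMI already provides one value. The 3-month EDE-Q provides the other only if transfer comes later; otherwise the last EDE-Q is the baseline one. One web EDE-Q at transfer would close that gap.
3. Report the whole stepped-care pathway alongside: all starters, at the end of all treatment and at follow-up. A value taken before transfer cannot speak to durability at 12 months, so this analysis has to carry that part for stepped-up patients.
4. Keep the split by treatment type as descriptive.
5. Use the same all-starters sample for the outcome models of research questions 2 and 3.
6. Reconcile the Study design statement on the minimum number of outpatient sessions with the step-up and withdrawal rules in Patient sample, so that it is clear when outpatient treatment ends for analysis.

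The cost is a few sentences and one extra questionnaire, which is a small addition to the assessment schedule; clinical care is unchanged. The last value before transfer is one defensible choice among several, so it should be fixed in advance. The downside is a likely smaller headline effect.

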### Control group

A healthy control group (consisting of 30-35 persons) will be recruited through advertisements and matched to the patient group in terms of age, gender, and length of education. In order to control for longitudinal changes, the control group will be tested twice, with an interval of 1 year. The control group will provide activity measures, blood and stool samples, and complete the EDE-Q.

### The intervention: CBT-E

The theory that underlies CBT-E is focusing on the mechanisms that maintain eating-disorder psychopathology rather than the processes that initially led to the development of the disorder (see a thorough overview of CBT-E [17]). CBT-E has the following four distinct treatment stages:The main priority in stage 1 is to engage the patient in treatment and behavioral changes. This stage includes creating a personalized formulation, establishing self-monitoring and in-session weighing, and introducing and establishing a regular eating pattern (at this point the therapist is not concerned about the quantity and composition of meals) and providing psychoeducation (on weight, weight changes, and eating disorders in general).Stage 2 is a brief transitional stage in which the therapist and the patient together review the treatment process, which should identify patients at risk of a poor outcome.Stage 3 is the main part of the treatment, whose aim is to address the core mechanisms that are maintaining the patient’s eating disorder (underweight, overevaluation of body shape and weight, and control over eating, dietary restraint and restriction, and event- and mood-triggered changes in eating).The aim in stage 4 is to ensure that the implemented changes are long-lasting, and to minimize the risk of relapse [17].

Sessions are provided twice weekly in stage 1, weekly in the subsequent stages, and biweekly toward the end of the intervention. One of the main goals of CBT-E treatment is to help the patient remain in the treatment program until it is completed. The treatment may end before it is completed if either the patient or the therapist decides to stop. If a patient wants to stop the treatment, the therapist will try to explore the reasons while focusing on the expectation that completing the treatment will produce a good outcome. If the patient then still wants to stop the treatment, it will be ended. The therapist will stop the treatment when it is concluded that the treatment is not working according to the plan. The therapist will always try to resolve these problems with the patient. If there are no acceptable solutions, the therapist will end the treatment before it is completed. When this happens the therapist will always try to make the patient understand why treatment is ending and also try to obtain mutual agreement that there are no other options.

### Intensive CBT-E

Intensive CBT-E treatment is performed on an inpatient basis and involves the same procedures and strategies as outpatient CBT-E, but it is more intensive. The method is described by [name] [51]. Each patient will work within a multidisciplinary team composed of a physician, a psychologist, a physiotherapist, and nurses. The use of assisted eating is one of the main differences from outpatient CBT-E [52]. The nurses and the rest of the staff at the unit are trained in CBT-E in order to be able to help the patient prepare for the meals and to help the patient use the tools of cognitive behavior therapy for eating disorders to identify and address the maintaining mechanisms of the eating disorders. Standard duration of the inpatient CBT-E is 13 weeks. Inpatient therapy can be prolonged if BMI is below 16 or if the patient has additional problems to address (e.g. comorbidity). After inpatient therapy the patient can have four to six weeks of day treatment before outpatient CBT-E is conducted. Expected weight gain during inpatient CBT-E is 1,0 – 1,5 kg per week until normal weight is established.

### Concomitant treatment

All patients are advised to take the following standard dietary supplements daily: two omega-3 capsules, a 500-mg calcium tablet, and a multivitamin tablet. Patients with severe clinical depression will be treated with antidepressants. Most patients will have depressive symptoms secondary to long standing underweight. This depression is usually moderate and is not treated with antidepressants. In case of depression that makes CBT-E ineffective, treatment is suspended until pharmacological antidepressive treatment is established and stable. Sometimes a decision to start antidepressants can be made before psychotherapy starts, but it might be necessary to try psychotherapy and observe whether the clinical depression makes CBT-E impossible to perform. If there are not specific contraindications, fluoxetine 20 mg a day is started, after one week dosage is increased to 40 mg and after another week fluoxetine is increased to 60 mg a day. The patient is assessed weekly for side effects. If 60 mg is well tolerated, antidepressant effects are usually observed two weeks after having started with 60 mg. If the patient experience unacceptable side effects, fluoxetine is stopped and other antidepressant is started, usually escitalopram. If fluoxetine is well tolerated but sufficient antidepressive effects are not observed olanzapine 5 mg is added.

If a patient receives additional psychological or somatic treatment for comorbid conditions, this will be recorded.

### The therapists

Each patient will be treated by a single therapist. All of the therapists are trained in CBT-E through individual weekly supervision by an experienced on-site CBT-E therapist in their first year of delivering CBT-E. In addition, to ensure that treatment is correctly implemented and delivered equally to all patients, weekly supervision meetings attended by all of the therapists will be held throughout the study. Each of the cases will be individually discussed at these 2-hour weekly meetings. All of the therapists have been participating in monthly video-conference supervisions performed by the international collaborators [name] and [name], and this supervision will continue throughout the study.

### Assessment and measurement points

The present study has five main assessment time points: at baseline (before treatment), at 3 months after starting treatment, at the end of treatment, at 20 weeks after ending treatment, and at 12 months after ending treatment. In addition, certain clinical measures will be recorded on a weekly basis, and early behavioral changes, treatment adherence, and therapeutic alliances will be measured at 4 weeks into treatment. Table 1 provides an overview of all of the study measures and their measurement time points. Most of the questionnaires will be completed using an Internet-based assessment platform, called CheckWare; the security of patient anonymity of this Web-based solution is approved by the Western Norway Regional Health Authority. The forms can be completed at home or on a computer in the clinic. The CheckWare program is creating e-mail reminders for the therapists when measurements are upcoming or delayed. The therapists schedule a time for the assessment at a computer in the clinic prior to a treatment session. The Web-based program immediately creates scores and diagrams based on the assessments that are reviewed by the therapist and patient together in the following session. Further, in the initial stages of the project there will be monthly meetings between research personnel and the therapists where feedback is given and potential problems with the data collection is discussed.

**Table 1 Tab1:** Overview of the study measures and their measurement time points

	Measure	Baseline before treatment	Weekly during treatment	4 weeks after starting treatment	3 months after starting treatment	End of treatment	20 weeks after ending treatment	12 months after ending treatment
Initial subject and disease characteristics	Sociodemographic background information and illness history	x						
	BMI	x	x	x	x	x	x	x
Eating-disorder diagnosis ﻿and comorbidity	EDE-Q	x			x	x	x	x
	Other mental-health diagnoses	x			x	x	x	x
	MINI 6.0.0	x				x		x
	Other somatic ICD-10 diagnoses	x			x	x	x	x
Eating behaviors	Days with regular eating		x					
	Weekly binge-editing episodes		x					
	Weekly purging episodes		x					
	Current medications	x			x	x	x	x
Blood sampling	Potassium	x			x	x	x	x
	Venous base excess	x			x	x	x	x
	Estradiol	x				x		x
	FSH	x				x		x
Blood sampling in biobank	Genetic and other relevant biomarkers	x			x	x	x	x
	BMD (DEXA)	x				x		x
	Work status	x			x	x	x	x
Psychometric measures								
	CIA	x			x	x	x	x
	BDI	x			x	x	x	x
	BAI	x			x	x	x	x
	RAND-36	x				x		x
	SCL-90-R	x				x		x
Treatment parameters	Measure of early adherence			x				
	WAI-S			x		x		
	Type of treatment (CBT-E or Intensive CBT-E)	x			x	x	x	x
	Active, finished, or dropped out	x			x	x	x	x
	Parallel psychological treatment (other diagnose)	x			x	x	x	x
Activity measures	Accelerometry	x				x		x
	Daily log of physical activity (over 7 days)	x				x		x
	EED	x				x		x
	CET	x				x		x
Stool sample in biobank	Bacteriological measures	x			x	x		x
	IBS self-report	x			x	x		x

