#### Working Alliance Inventory–Short Form

The WAI-S (Working Alliance Inventory–Short Form) is a 12-item self-report measure of the general alliance in therapy and three different specific aspects of the therapeutic alliance: bonds, goals, and tasks. This measure has both patient and therapist versions, and it has been found to exhibit acceptable validity and interrater reliability [70–72]. This instrument will be administered at 4 weeks into treatment and at the end of treatment.

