#### Checklist for dropout interviews

The checklist for dropout interviews will include specific items asking patients whether or not they agree with statements about reasons for ending treatment, including motivation, dislike of the treatment form, being satisfied with their current status, feeling able to continue on their own, not being satisfied with the treatment results, finding the tasks during treatment too difficult, having problems relating to the therapist, having difficulties due to the presence of other illnesses, and having practical problems related to work, studies, family relationships, and finances. The interview will also ask a general question about other reasons, and it will be conducted by a study secretary via telephone within a few weeks of the treatment ending prematurely.

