#### Study setting

The SED is a regional unit for the most severely ill eating-disorder patients in Western Norway. This unit serves a population of 1 million inhabitants. Since 2007, all therapists at the SED have contributed to comprehensive data collection as part of internal quality control. As a follow-up and extension of this work, a Regional Research Database (Western Norway) for eating disorders has been designed, which is located at the SED. This database has been approved by the Norwegian Data Inspectorate, and data collection was commenced in January 2016. The present study will use data from this database in addition to measures specifically added to test the hypotheses of this study. The present study has been designed in close collaboration with the therapists at the SED in order to ensure that it will be possible for them to perform the data collection. The process assessments included in the present study are already embedded in the clinic and are applied in clinical practice.

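### The week-4 patient-rated alliance score is not exempted from the joint therapist–patient score review, so the alliance predictor in research question 3 may be biased by expected disclosure

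*Protocol article*

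**What the plan says.** Assessment and measurement points describes the data flow. "Most of the questionnaires will be completed using an Internet-based assessment platform, called CheckWare". Forms may be filled in at home or in the clinic, and for the clinic: "The therapists schedule a time for the assessment at a computer in the clinic prior to a treatment session". The platform then "immediately creates scores and diagrams based on the assessments that are reviewed by the therapist and patient together in the following session". The section names no questionnaire to which this does not apply. Its one statement touching confidentiality is that "the security of patient anonymity of this Web-based solution is approved by the Western Norway Regional Health Authority". That concerns the security of the system and does not say that any rating is withheld from the treating therapist.

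The section Working Alliance Inventory–Short Form describes a 12-item self-report scale covering bonds, goals and tasks. "This measure has both patient and therapist versions, and it has been found to exhibit acceptable validity and interrater reliability". On timing: "This instrument will be administered at 4 weeks into treatment and at the end of treatment". Neither this section nor Table 1 says how the form is completed or who sees it. Study setting adds: "The process assessments included in the present study are already embedded in the clinic and are applied in clinical practice".

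The therapists section assigns one therapist to each patient. Research question 3 uses early alliance, together with early behavioural change and adherence, to predict pre-post outcome and dropout.

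**The concern.** Read together, these sections leave a patient who is unhappy with the therapist at week 4 to record this on a form that the two of them may look at in the next session. The low end of the alliance scale is where one would look for later dropout, and it is also the end a patient has most reason to avoid when the rated person will see the answer.

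The bias would come from expecting the review, not from the review itself, which takes place after the rating. If some patients move low ratings upward, scores gather at the favourable end and the ordering among dissatisfied patients is partly lost. A weak or absent association between patient-rated alliance and outcome or dropout would then be hard to interpret, because a true absence and a concealed signal would look the same. The Background, in its paragraph on therapeutic alliance, treats this link as unsettled in anorexia nervosa, so an ambiguous null result would add little.

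**Working it through.** **1. Does the joint review cover the patient WAI-S?**
- The review rule is general and has no exemption (Assessment and measurement points).
- The platform carries most questionnaires, and those on or off it are not listed (same section).
- The WAI-S section and Table 1 give timing only.
- Process assessments are already applied in clinical practice (Study setting), and no separate route is described for the WAI-S.

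Coverage is therefore the natural reading, but it is not stated.

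**2. Is the reviewer the person rated?** Yes, if the form is covered, because each patient has a single therapist.

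**3. Can the effect be sized from the documents?** No. They give no mean, standard deviation, reliability or ceiling rate for the WAI-S. The form of the distortion also matters. A uniform upward shift leaves a correlation unchanged. Attenuation needs loss of ordering, or a smaller spread of real differences against the same measurement error.

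**4. Illustration A (all inputs assumed).** True correlation of alliance with outcome 0.30; reliability 0.85, falling to 0.60 or 0.40; n = 75. That n is not stated in the protocol, though it equals 100 × (1 − 0.25), the recruitment target less the dropout probability used in Power analyses.

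Observed r = 0.30 × √reliability:
- 0.30 × √0.85 = 0.277
- 0.30 × √0.60 = 0.232
- 0.30 × √0.40 = 0.190

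Two-sided 5% power by Fisher's z ≈ Φ(atanh(r) × √(n − 3) − 1.96):

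| Reliability | Observed r | Power, n = 75 | Power, n = 100 |
|---|---|---|---|
| 0.85 | 0.277 | 0.67 | 0.80 |
| 0.60 | 0.232 | 0.52 | 0.64 |
| 0.40 | 0.190 | 0.37 | 0.47 |

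To see how severe these cases are, hold error variance at 0.15 and shrink the spread of real differences by a factor b. Reliability is then 0.85b² / (0.85b² + 0.15).
- Reliability 0.60 needs b² = (0.60 × 0.15) / (0.40 × 0.85) = 0.265, so b = 0.51.
- Reliability 0.40 needs b² = (0.40 × 0.15) / (0.60 × 0.85) = 0.118, so b = 0.34.

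The real spread would have to fall to about a half or a third, so these are strong scenarios.

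**5. Illustration B (starting from the protocol's regression sample size).** Power analyses states 81 subjects for 80% power at two-sided 5%. A single-coefficient t test reproduces N = 81 (power 0.803) with f² = 0.10, that is R² = 0.10/1.10 = 0.091. Let the alliance score keep a share λ of that R², with f² = λR² / (1 − λR²):

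| λ (assumed) | Power at N = 100 | N for 80% power |
|---|---|---|
| 1.0 | 0.88 | 81 |
| 0.9 | 0.84 | 91 |
| 0.8 | 0.79 | 103 |
| 0.7 | 0.73 | 118 |
| 0.5 | 0.58 | 167 |

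A mild loss costs little; only a large one matters. Both illustrations concern a continuous outcome and say nothing directly about dropout, which is binary.

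**The case against.** The strongest objection is that the decisive fact is absent. The article never says that the WAI-S is on the platform. The Discussion mentions a separate, detailed data-collection protocol written with the therapists, and who sees which form would naturally be settled there. This stands to the extent that a missing list of instruments is no fault in an article. It does not remove the point, because the article does state a general rule of joint review, and that rule carries no exemption for the one questionnaire that rates the reviewer.

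Two further objections stand. The consequence is narrow: patient-rated alliance is one of three early predictors in a non-primary question, a therapist version of the scale exists, and the end-of-treatment WAI-S is not the early predictor. Joint review also has a purpose, since the Discussion wants assessments to be meaningful to patients and therapists so that data are not missed.

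Some stronger readings are tempting but unsupported:
- A reader might infer that alliance scores will be compressed. The documents show no such thing, and the Background cites studies that found quite a strong alliance in this population, so high scores need not be an artefact.
- A reader might take the dropout checklist, whose items include "having problems relating to the therapist" and which a study secretary administers by telephone, as proof that the authors thought therapists unsuitable for such questions. That interview takes place after treatment has ended early, when there is no next session, so it shows only that a non-therapist route is available.
- A reader might extend the argument to the primary EDE-Q. Its scores exist only once the form is submitted, so withholding them until then would change nothing, and the 20-week and 12-month assessments come after treatment has ended.

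**Conclusion.** The point holds in limited form. On the natural reading, patients rate their only therapist at week 4 expecting that therapist to see the score. This may push ratings upward and narrow their spread, and so weaken the association of patient-rated alliance with outcome and dropout in research question 3.

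The conclusion rests on two assumptions: that the patient WAI-S is among the questionnaires on the platform, and that expected disclosure changes how some patients answer. The size cannot be derived from the documents. The power figures show only what would follow from assumed losses, and they range from slight to substantial. For dropout even the direction is not certain, because a therapist who has seen the score may also take part in the decision to end treatment. The evaluation of CBT-E on the primary outcome does not use the WAI-S and is unaffected.

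**What to change.** In Assessment and measurement points, state that the week-4 patient WAI-S is excluded from the joint score review, goes directly to research staff and is not shown to the therapist. Put one sentence on the form telling patients so, since the protection works only if they know of it. If the form is already handled this way, saying so closes the point. Leave the EDE-Q and the other questionnaires as they are.

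The cost is a display setting in the platform and a line of text. The real downside is that therapists lose the patient's week-4 alliance score as feedback, which slightly changes a routine in a study of ordinary practice. The matter is best settled before ratings are collected, because analysis cannot remove disclosure bias from those already given. If some have been collected under joint review, record the date of the change so that the two sets can be told apart.
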